### **12.2 Sample Size Determination**

*Sample Size.* We derived the sample size that is needed to detect an overall difference which is of clinical significance and with potential cost-saving implications. We have powered our study to detect the primary outcome (10% relative reduction in overall hospital admissions and overall ED visits) at 12 months. We estimate 1,500 BACO members are eligible intermediate risk patients. We know from existing institutional data that these intermediate risk BACO members experience an average of 4.3 inpatient admission over 12 months, and 10.2 ED visits over 12 months. With these baseline data, we estimate that a total sample size of 364 patients (N=182 in each arm) is adequate to detect a 10% reduction in total ED plus hospital visits with statistical power of 0.90 and two-sided type I error rate of 0.05, accounting for 80% retention over a 12-month study period.

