| Duration of follow-up | 12 months                                                                                                                                                                                                                                                                                                                                                                                                                                                                                                                                                                                                                                                                                                                                                                                                                                                                                                                                                                                                                                                                                                     |
| Criteria for efficacy | 
Measures:
We collect data on demographics (age, gender, race, ethnicity, and language), insurance coverage (proportion of days covered from claims data), and on potential confounding variables, such as medical comorbidity as measured by a validated comorbidity index (the Charlson Comorbidity Score), mental health and substance use diagnoses, health-related social needs screening results, and medication adherence using a measure of proportion of days covered based on pharmacy claims data.
 
Primary end points:
Our primary outcome is the percentage change in all-cause hospital admissions and all-cause emergency department visits (a composite outcome) in the 12 months following enrollment.
 
Secondary end points:
Secondary outcomes include all-cause hospital admissions and all-cause emergency department visits as separate outcomes, all-cause 30-day hospital readmissions, 30-day ED revisit rates, and connection to resources (referral to food pantry, visits to food pantry, utility shutoff protection letters).
 |

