|  | 
categorical variables. Due to a potential high number of patients with zero-count visits (136 out of 364, 37%), we employ a zero-inflated negative binomial model, which is a two-part model that examines simultaneously the odds of any visit, and the rates of visits among those patients who have any health care utilization. We use Bayesian Information Criteria as the model goodness-of-fit measure to compare zero-inflated negative binomial model with other models for the rates outcomes, including over-dispersed Poisson model, and negative binomial model. As a sensitivity analysis, we also model only the binary outcome of any utilization using logit link function. In the adjusted regression models, we will control for any factors including baseline utilization that are found statistically significant between the two arms. We report odds ratios and 95% CI for binary outcome (e.g., any visit) and rate ratios for the outcomes of inpatient and ED visits. We also compare the secondary outcomes of health-related social needs (e.g., connected to community-based partner; received services through referral to community partner; referrals and visits to hospital food pantry; received utility shutoff protection letter) between the two arms and examine adjusted intervention effect using logistic regression with odds ratio and 95% CI.
 
The primary analyses will be based on intent-to-treat. Because participants may receive varying “doses” of the intervention, we will also analyze the intervention effect according to whether participants received a minimum dose of the intervention. If the pharmacy liaison-patient navigator documents in their first telephone assessment that the patient has received the THRIVE screening in the past three months, and rescreens the patient if they have not been screened in the past three months, we consider the patient to have received the minimum intervention dose.
 |

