## **5. Primary outcome analysis**

### **5.1 Definitions**

Our primary outcome is all-cause hospital admissions and all-cause emergency department visits (a composite outcome) in the 12 months following enrollment. We compare baseline characteristics of participants using two-sample t tests for continuous variables or Chi-square tests for categorical variables. We assess the distribution of the outcome variables, diagnose error terms in residual analysis, and use appropriate link functions (e.g., normal link function for continuous outcomes with normal distribution) to construct linear regression models to assess the treatment effect. We will further assess any potential collinearity among covariates by evaluating variance inflation factors and correlation matrices. In the case where there are excess zeros (e.g., no visits), we employ a zero-inflated negative binomial model, which is a two-part model that examines simultaneously the odds of any visit, and the rates of visits among those patients who had any health care utilization. In the adjusted regression models, we will control for any factors including baseline utilization that are found statistically significant between the two arms.

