## **5.4 Calculation of the outcome**

A composite measure is created by summing all-cause hospital admissions and all-cause emergency department visits (a composite outcome) in the 12 months following enrollment.

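### The primary zero-inflated model is described with hurdle-model parameters, and no single contrast on mean total 12-month visits is named as the primary test

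*Combined protocol and SAP*

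**What the plan says.** **The question.** Protocol 12.2 powers the trial for a "10% relative reduction in overall hospital admissions and overall ED visits" at 12 months, from baseline means of "4.3 inpatient admission over 12 months, and 10.2 ED visits over 12 months", with "statistical power of 0.90 and two-sided type I error rate of 0.05". Protocol 12.3 and SAP 5.3.2 compare the arms on average visits after enrollment. SAP 5.4 builds the outcome as a count: "A composite measure is created by summing all-cause hospital admissions and all-cause emergency department visits". Protocol 12.3 and the SAP synopsis (Primary end points) word it differently: "Our primary outcome is the percentage change in all-cause hospital admissions and all-cause emergency department visits (a composite outcome").

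**The model.** The SAP synopsis (Statistical method) cites 136 of 364 patients with zero counts and adopts a zero-inflated negative binomial, "which is a two-part model that examines simultaneously the odds of any visit, and the rates of visits among those patients who have any" utilization. SAP 5.1 describes it in the same way but uses it only if zeros are excessive, with no threshold. Before that, 5.1 would "use appropriate link functions (e.g., normal link function for continuous outcomes with normal distribution) to construct linear regression models to assess the treatment effect". Protocol 12.3 has only this linear-model text.

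**Model comparison and reporting.** The synopsis adds: "We use Bayesian Information Criteria as the model goodness-of-fit measure to compare zero-inflated negative binomial model with other models for the rates outcomes". The alternatives are an over-dispersed Poisson and a plain negative binomial. It then promises odds ratios for binary outcomes and rate ratios for visits, with a separate logit model of any utilization as a sensitivity analysis. No passage names a deciding coefficient, a joint test, a contrast of overall means or a multiplicity rule.

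**The concern.** The trial asks one question, whether THRIVE+ lowers the mean number of acute visits. The model as described returns two treatment effects, neither of which is the effect on that mean. Both also carry labels that belong to a different model. An analyst who follows the plan exactly can report an odds ratio as one for any visit when it concerns a latent class, and a rate ratio as one among users when it covers everyone outside that class.

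Because no deciding result is named, a favourable result in one part and a null or adverse result in the other has no agreed interpretation. The BIC comparison has no stated consequence, and linear models are still in the text, so the primary analysis is not tied to one model either.

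**Working it through.** **Inputs from the documents.** Zeros: 136/364 = 0.374 (SAP synopsis), taken here as 12-month composite counts because the SAP does not state the period. Mean: 4.3 + 10.2 = 14.5 visits (Protocol 12.2). Effect: 10% relative, so 1.45 visits. Two-sided 0.05, power 0.90, 80% retention.

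**Assumed.** Dispersion k, which neither document gives; it is varied below. The control arm is given the 37.4% zeros and the mean of 14.5.

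**1. The stated sample size.** n = 2 × 14.5 × (1.960 + 1.282)² / 1.45² = 144.9, so 145 per arm. Then 145/0.8 = 181.25, so 182, as stated. This needs variance equal to the mean, which is inferred. It is one comparison of mean total visits, not a test of a zero-inflated coefficient.

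**2. What the model estimates.** Let π be the structural-zero probability, μ the count-part mean and q = (1 + kμ)^(−1/k) the chance that an at-risk patient has no visit.
- P(no visit) = π + (1 − π)q
- P(any visit) = (1 − π)(1 − q)
- Mean among users = μ/(1 − q)
- Overall mean = (1 − π)μ

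The logit coefficient concerns π and the count coefficient concerns μ. A hurdle model would give P(any visit) and the distribution among users. The primary question concerns (1 − π)μ.

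**3. A 10% lower mean acting only through π.** Solve for π₀ with 37.4% zeros and overall mean 14.5; then 1 − π₁ = 0.9(1 − π₀).

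| k | μ | π₀ | π₁ | Structural-zero OR | No-visit OR | Count rate ratio |
|---|---|---|---|---|---|---|
| 0.5 | 23.0 | 0.370 | 0.433 | 1.30 | 1.30 | 1.00 |
| 1 | 22.1 | 0.345 | 0.411 | 1.32 | 1.30 | 1.00 |
| 2 | 19.5 | 0.256 | 0.330 | 1.43 | 1.30 | 1.00 |

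At k = 2 the structural-zero odds go from 0.256/0.744 = 0.344 to 0.330/0.670 = 0.493, a ratio of 1.43. P(no visit) goes from 0.374 to 1 − 0.9 × 0.626 = 0.436, so its odds go from 0.596 to 0.774, a ratio of 1.30.

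**4. The reverse case.** With a count rate ratio of 0.70 and no effect on π, the logit part shows 1.00. The true odds ratio for any visit is 0.985 at k = 0.5 and 0.91 at k = 2. The ratio of means among users is 0.704 and 0.73.

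**5. Two tests.** If significance in either part counted, 1 − 0.95² = 0.0975. Null simulations (182 per arm, 500 runs per scenario, assumed parameters) gave 9.4% to 10.2%, with Monte Carlo error of about 1.3 points.

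**6. Opposing effects.** Take π = 0.25, μ = 6.67, k = 1, a count rate ratio of 1.2 and a structural-zero odds ratio of 1.6. Structural-zero odds become 0.333 × 1.6 = 0.533, so π₁ = 0.348. The overall mean ratio is 0.652 × 1.2/0.75 = 1.04. At least one part was significant in 52% of 300 runs, although the overall mean hardly changed.

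**7. BIC.** Across the simulated scenarios BIC preferred the zero-inflated model in 72% to 100% of runs. If BIC did select the model, the reported effect would depend on the data.

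**The case against.** The case for leaving the plan largely alone has substance.

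- **The labels may do little harm.** At dispersion 0.5 and mean 14.5 the two odds ratios agree to two decimals. This stands: the error in kind is certain, but its numerical size is not. A reader might quote a gap of over 20% by comparing odds levels: with count mean 8 and dispersion 0.8 (both assumed), structural-zero odds are 0.466 against 0.596 for no visit. The SAP reports odds ratios, however, and for a 10% lower mean acting through the zero part these are 1.35 against 1.30, about 4% apart.
- **The effect would not be hidden.** Where the count rate ratio is 1.00, the logit part still moves. The separate logit model estimates the odds of any utilization correctly, and if the reported odds ratio comes from it, the label is right. The SAP does not say which model supplies it.
- **No either-part rule is stated.** This is correct, so 9.75% is the consequence of one possible reading and not a property of the SAP.
- **BIC.** A reader might infer that BIC replaces the primary model. The text only compares models and gives no selection rule. Nor is BIC shown to be undefined for the over-dispersed Poisson, since the SAP does not say that quasi-likelihood is used.
- **Percentage change.** A reader might call it undefined for patients with no prior visits, but a group-level reading is available. The defect is inconsistent wording.
- **SAP 5.1 as a decision path.** Inspecting the distribution and using the zero-inflated model if zeros are excessive is a fair reading. It still has no threshold and ends without a deciding contrast.

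**Conclusion.** The concern holds. As written, the plan attaches hurdle interpretations to zero-inflated coefficients and gives no single test of the quantity it was powered for. Neither conclusion needs an assumed figure.

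The size is conditional. With 37.4% zeros, mean 14.5 and a 10% reduction acting only through the zero part, the odds-ratio label is off by nothing visible at dispersion 0.5 and by 1.43 against 1.30 at dispersion 2. The count rate ratio shows no effect at all. Type I error of about 9.75% applies only if success in either part is accepted. The documents do not support saying that the reported ratios will be badly misread, that the false-positive rate is already doubled, or that BIC will change the primary model. They leave each of these open, which is reason enough to settle the primary contrast in the text.

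**What to change.** 1. Name one primary contrast: the ratio of mean total 12-month visits, zeros included, with one two-sided test at 0.05 that the BIC comparison does not change.
2. Name the one model that supplies it. A negative binomial log-link regression with robust standard errors would do. So would the marginal ratio of (1 − π)μ from the zero-inflated model with a suitable confidence interval. If the negative binomial is chosen, robust errors matter: its ordinary likelihood-based test rejected in only 0.2% to 2.4% of the zero-inflated null simulations.
3. Make the two-part results secondary. Either label them as effects on structural zeros and on the at-risk count, or fit a hurdle model (logistic plus zero-truncated negative binomial) if any visit and visits among users are the quantities wanted. State which model supplies each reported odds ratio.
4. Define the endpoint throughout as the summed 12-month count in place of percentage change, and remove the linear-model text for this outcome.
5. Acknowledge that the zero count (136 of 364) was already known when the model was fixed; this applies to whichever model is now chosen.

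The cost is SAP wording and a few lines of SAS. The downside is that the two-part description of zeros becomes secondary.

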### **3.2 Definition of the analysis population**

Study recruitment took place from May 2019 through March 2020 at a large primary care internal medicine practice affiliated with an academic safety-net hospital in Boston, Massachusetts. Patients that qualified for the hospital's pharmacy care program were eligible for the study. Eligibility criteria for the program were: 1) age 18–64; 2) within the 3rd to 10th percentile for health care utilization and cost among Medicaid Accountable Care Organization (ACO) membership at the time of enrollment into the pharmacy program; and 3) attended a visit with a primary care provider (nurse practitioner or physician).

### **3.3 Sample size**

We used internal health care utilization data from the institution for sample size calculation. Using a two-sided type-I error rate of 0.05, a sample size of 364 patients (N=182 in each arm) would achieve 90% power to detect a 10–percentage point reduction in our primary outcome of total emergency department visits plus inpatient hospital admissions.

## **4. Analysis principles**

### **4.1 General principles for analysis of outcomes**

The primary analyses are based on intent-to-treat. Because participants may receive varying “doses” of the intervention, we also analyze the intervention effect according to whether participants received a minimum dose of the intervention.

In order to assess whether the presence of comorbid mental health and substance use diagnoses, race, and language may modify the treatment effect, we will evaluate interaction terms between these pre-determined potential moderators and the treatment variable in the overall sample, and further conduct stratified analyses among these potential modifiers to assess the robustness of any differential effects due to effect modification.

### **4.2 Participants' characteristics at inclusion**

Table 1 shows descriptive characteristics for the usual care and enhanced usual care groups. The usual care and enhanced usual care groups differed in the respective proportion who spoke English (78% vs. 87%), reported housing insecurity (9% vs. 13%), received a referral to the hospital food pantry in the past 12 months (14% vs. 25%), had at least one visit to hospital food pantry in past 12 months (12% vs. 20%) and had a diagnosis of PTSD (21% vs. 14%). The majority belonged to a racial/ethnic minority group, and 96% had received screening for health-related social needs in the past year. Approximately two-thirds of patients had significant medical comorbidity, and nearly half carried a diagnosis of depression.

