## **6.2 Methods for analysis**

We will use similar methodology above to examine bivariate comparison and conduct adjusted analyses to examine the secondary outcomes.

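### Food-pantry referral and visits already favour THRIVE+ at inclusion, yet the SAP neither guarantees adjustment for each measure's baseline value nor says that the adjusted result leads

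*Combined protocol and SAP*

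**What the plan says.** **Baseline.** Among the characteristics on which the arms differed, SAP 4.2 gives the proportions who "received a referral to the hospital food pantry in the past 12 months (14% vs. 25" per cent) and who "had at least one visit to hospital food pantry in past 12 months (12% vs. 20" per cent). Usual care comes first in each pair, so both measures are higher in the enhanced (THRIVE+) arm.

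**Outcome status.** The SAP synopsis, under secondary end points, includes "connection to resources (referral to food pantry, visits to food pantry, utility shutoff protection letters". Its statistical-method row again names pantry referrals and visits among the secondary outcomes. SAP 6.1 keeps visits but omits referral. Protocol 4.2.2 and Table 2 class these measures as post-hoc, taken from the clinical data warehouse at 12 months.

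**Analysis.** For these outcomes the synopsis plans a comparison between arms and an adjusted logistic model reported as an odds ratio with 95% CI. SAP 6.2 says: "We will use similar methodology above to examine bivariate comparison and conduct adjusted analyses to examine the secondary outcomes". Neither place says which result is the main one.

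**Covariates.** SAP 5.1 states that "we will control for any factors including baseline utilization that are found statistically significant between the two arms"; the synopsis and SAP 5.3.2 repeat this. SAP 5.3.2 also speaks of controlling for possible baseline differences and for covariates fixed in advance, with age and gender as its only examples.

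**The concern.** The value of a measure in the year before enrolment is plausibly a strong predictor of the same measure in the year after. It belongs in the model for that reason, whatever the p-value of the baseline comparison. A between-arm test answers a different question and may leave the covariate out.

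Here the imbalance runs in the direction of the hoped-for effect. An unadjusted comparison at 12 months would contain whatever part of the earlier gap persists, and would credit that part to the intervention. Connection to resources is the mechanism put forward in the hypotheses (protocol 12.1), so a spurious difference on it would matter to the reading of the trial even though it is not the primary outcome.

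**Working it through.** **Inputs.** Baseline rates come from SAP 4.2. The arm size comes from SAP 3.3 ("a sample size of 364 patients (N=182 in each arm) would achieve 90% power"). The synopsis count of "zero-count visits (136 out of 364, 37" per cent) supports a total of 364, but realised arm sizes are not given, so 182 per arm is an assumption. The named test is the chi-square, at a level of 0.05; no continuity correction is mentioned.

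**The plan's own figure.** The documents give no p-value or odds ratio for these imbalances. The 182 per arm is reproducible from protocol 12.2 ("statistical power of 0.90 and two-sided type I error rate of 0.05, accounting for 80% retention over a 12-month study period") if the SD is assumed to be Poisson, √14.5, because no SD is stated: n = 2 × (1.960 + 1.282)² × 14.5 / 1.45² ≈ 145, and 145 / 0.80 = 181.25, rounded up to 182. It enters here only as the arm size.

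**Step 1: size of the gap, from the rounded percentages.**
- Referral: (0.25/0.75) / (0.14/0.86) = 2.05.
- Visits: (0.20/0.80) / (0.12/0.88) = 1.83.

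**Step 2: would the significance rule select the baseline value?** With 182 per arm, the percentages allow 25–26 against 45–46 for referral and 21–22 against 36–37 for visits. Pearson chi-square = N(ad − bc)² / product of margins.

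| Measure | Counts | Pearson p | Yates p | Fisher p |
|---|---|---|---|---|
| Referral | 25 vs 46 | 0.005 | 0.008 | 0.008 |
| Referral | 26 vs 45 | 0.012 | 0.017 | 0.017 |
| Visits | 21 vs 37 | 0.022 | 0.032 | 0.031 |
| Visits | 22 vs 36 | 0.045 | 0.063 | 0.062 |

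These are the extremes; the other count pairs lie between them. Worked case, 22 vs 36: 364 × (22×146 − 36×160)² / (182×182×58×306) = 364 × 2548² / 587,884,752 = 4.02, p = 0.045. With Yates, 2548 becomes 2366, chi-square is 3.47 and p = 0.063.

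Unequal arms totalling 364 were tried from 164/200 to 200/164. Pearson p for referral never exceeds 0.015. For visits it reaches 0.060 with 164 in usual care and 200 in the enhanced arm, and stays below 0.05 in the other splits tried.

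**Step 3: what the unadjusted comparison shows with no treatment effect.** Let s1 and s0 be the probability of the event in follow-up for patients with and without it before enrolment, the same in both arms. The follow-up rate in an arm with baseline rate b is s1·b + s0·(1 − b). The documents give no persistence, so s1 and s0 are assumed. Example, referral at 0.4/0.10: usual care 0.056 + 0.086 = 0.142, enhanced 0.100 + 0.075 = 0.175, OR = (0.175/0.825)/(0.142/0.858) = 1.28.

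| s1 / s0 | OR, referral | OR, visits | Unadjusted rejection, referral | Unadjusted rejection, visits |
|---|---|---|---|---|
| 0.4 / 0.10 | 1.28 | 1.21 | 13% | 8% |
| 0.6 / 0.08 | 1.47 | 1.36 | 28% | 14% |
| 0.8 / 0.05 | 1.70 | 1.54 | 58% | 23% |
| 1 / 0 (complete) | 2.05 | 1.83 | not run | not run |

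Rejection rates are two-sided at 0.05, from 20,000 simulated trials per row, conditional on baseline counts of 25 vs 46 (referral) and 22 vs 36 (visits). Nearly all rejections favour THRIVE+. A Mantel-Haenszel test stratified on the baseline value rejects in 4.8% to 5.2% of trials in every scenario.

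**The case against.** The strongest reply is that the plan would adjust anyway. The SAP names a chi-square test without a correction, and with 182 per arm that test is below 0.05 for every count compatible with the printed percentages, for both measures. The synopsis already specifies an adjusted odds ratio for exactly these outcomes, and SAP 5.3.2 has softer wording on baseline differences that does not rest on a test. Most of this stands. A reader might infer that selection is on a knife-edge for both measures; for referral it is not, under any test tried.

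The reply does not close the point. It protects only the adjusted model, and SAP 6.2 leaves the bivariate result equally available as the finding. For visits, selection still turns on an unstated correction or on the realised arm sizes. The list in SAP 4.2 does not show what was selected either: at 182 per arm, two other characteristics on it, housing insecurity (Pearson p 0.18 to 0.31) and PTSD (0.054 to 0.098), would fail the rule.

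Two further objections have some force. The protocol treats these measures as post-hoc, which lowers their weight. And a covariate rule written after seeing SAP 4.2 is informed by the data, so the stated reason for it should be prognosis, not the observed gap.

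**Conclusion.** The point holds at modest severity. Adjustment for baseline referral is expected under the plan's own rule. Adjustment for baseline visits is likely but not guaranteed. The planned unadjusted comparisons carry the baseline gap whatever the rule selects. Without any effect, they would show odds ratios of roughly 1.2 to 1.7 in favour of THRIVE+. These sizes rest on 182 per arm and on assumed persistence.

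Three stronger readings are tempting and are not supported:
- That an odds ratio near 2 would arise with no effect. This needs complete carry-over from one year to the next, so it is an upper bound.
- That the look-back year may run past enrolment and the gap is already an intervention effect. The figures stand under characteristics at inclusion, and nothing in the documents points to overlap. The direction of the gap is not evidence of it.
- That the gap would feed the protocol's measure of connection to food. That is a separate intermediate outcome from the community partner's data (Table 1), not from the clinical data warehouse.

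**What to change.** In SAP 6.2, state that:
- each pantry outcome is analysed by logistic regression including its own value in the 12 months before enrolment, whatever the baseline p-value, because it is expected to predict the outcome;
- the odds ratio and 95% CI from that model are the main reported result, and the bivariate comparison is descriptive.

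In the same edit, reconcile protocol 4.2.2 and Table 2, the SAP synopsis and SAP 6.1 on whether referral and visits are secondary or post-hoc, and on whether referral is an outcome at all. Replace the two covariate rules in SAP 5.1 and 5.3.2 with one, so that the reference in SAP 6.2 to the methods above has a single meaning.

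The cost is SAP wording and one added covariate per model. The baseline values are already tabulated and no new data are needed.
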